## **Trial Procedures**

### Assessments prior to experimental protocol

*Screening Eligibility:* Individuals with cognitive impairment or limited English proficiency, as identified at the onset of telephone contact, will not undergo screening phone interview. After verbal consent for a screening interview, interviewers will conduct an approximate 20-minute survey using a scripted telephone interview format as previously described  to assess demographic information and screen for the presence of insomnia or not using the Pittsburgh Sleep Quality Index (PSQI). Eligibility questions will also evaluate whether current depression is absent and exclude subjects who answer affirmatively to the following two screening

question: “Are you depressed nearly every day for two weeks or more?” and/or “Have you lost interest in normal activities nearly every day for two weeks or more?”, using items from the 10-item Center for Epidemiologic Studies Depression . If subjects do not evidence symptoms of current depression, they will be advanced to interview assessment, in which the SCID-5 will be administered to confirm the absence of current depression using DSM-5 diagnostic criteria . In addition, we will screen for ongoing medical conditions and current use of medications such as antidepressant medications.

*Baseline eligibility:* At the onset of this interview assessment, written informed consent is obtained after reviewing any study-related questions. This baseline eligibility assessment is a face-to-face interview format lasting about 120 minutes, including the following assessments: SCID-DSM-5 (those with current psychiatric disorder or depression in last year will be excluded) and the DSISD ; demographic information and medical / medication histories including recent (last two weeks) infection and Charlson Co-Morbidity Index  and Chronic Disease Scale; substance use history; Mini-Mental Status Examination (those who score 24 or less will be excluded) ; height and body weight for calculation of body mass index, vital signs, blood sampling for screening laboratory tests (i.e., complete blood cell count, comprehensive metabolic panel, hemoglobin A1c, and Free T4 Index), and electrocardiogram (those with clinically significant abnormalities will be excluded).

A wrist actigraph and instructions for completing sleep diaries for a two-week period to monitor sleep wake patterns will be reviewed. Additionally, a Watch-PAT device will be worn for one night (those with sleep apnea and nocturnal myoclonus will be excluded) .

*Baseline assessment of clinical and other background variables.* The following baseline measures are assessed prior to the experimental protocol, but not repeatedly during the experimental protocol. Measures repeatedly assessed during the experimental protocol are described in the “Outcomes” section below.

Insomnia assessment: In addition to diagnostic evaluation of the presence of current DSM-5 insomnia disorder or not, duration and lifetime history of insomnia will be evaluated; profile of inflammatory activation may be related to duration of insomnia. Current severity of insomnia complaints will be evaluated by the Insomnia Severity Index (ISI) ) and the PSQI . These self-report data are in addition to the daily sleep diary  as completed by an Online Sleep Diary System, accessible via computer interface with unique user IDs, and objective assessment of sleep behaviors and sleep duration by wrist actigraphy. Sleep apnea will be screened by the Berlin Questionnaire  with objective evaluation using the WatchPat. . Sleep wake schedule will be evaluated using the Munich Chronotype Questionnaire  and daytime dysfunction associated with insomnia is assessed by the Fatigue Symptom Inventory (FSI)  and Multidimensional Fatigue Symptom Inventory-Short Form (MFSI-SF) .

Depression assessment: The SCID-5 interview will be used to determine the presence of past history of depression, and the absence of current depressive disorder and other psychiatric diagnoses. For depression history, we will identify number of episodes, age of onset, last episode, and treatment variables. Administration of the SCID is performed by interviewers who are trained to criterion validity; diagnoses is determined in a weekly consensus meeting to maintain reliability and criterion validity. Depressive/anxiety symptom severity is assessed at only baseline using the Patient Health Questionnaire-9 , Beck Depression Inventory-II , Beck Anxiety Inventory , General Anxiety Disorder-7 , and Inventory for Depressive Symptoms-Self Report .

Social domain: Social support measures include Social Provision Scale , Experiences in Close Relationships Questionnaire , and Interpersonal Support Evaluation List .

Psychosocial stress: Psychosocial stress is evaluated by Perceived Stress Scale , and childhood adverse psychosocial stress is evaluated using the Risky Families Questionnaire .

Health factors: Health variables, in addition to eligibility, include level of physical activity (i.e., Godin Leisure-Time Exercise Questionnaire)  and health functioning (i.e., Medical Outcomes Study Short-form (SF-36) .

#### Endotoxin vs. placebo administration methods

Following baseline assessments, inclusion and exclusion criteria will be examined and confirmed by the study physician ([name]). The study is conducted at the UCLA Clinical Translational Research Center (CTRC). Beginning at 8 am, a CTRC nurse, blind to the randomization schedule, will assess height and weight as well as vital signs (blood pressure, pulse, temperature). As noted above, participants will be excluded if: (a) blood pressure is less than 90/60 mmHG or greater than 160/120 mmHG, (b) pulse is less than 50 beats/minute, or (c) temperature is greater than 99.5°F. An indwelling venous catheter with a heparin lock will be inserted into the participant's dominant forearm for hourly blood draws and one into the nondominant forearm for a continuous saline flush (150 cc/h) for endotoxin vs. placebo administration. Baseline assessment of outcomes including self-report questionnaires and experimental affective response tasks will then be completed, followed by baseline blood sampling which is obtained about 60 minutes after placement of catheter and 30 minutes after completion of questionnaires and tasks. The CTRC pharmacy will receive the randomization assignment and prepare the endotoxin vs. placebo. After 90 minutes following arrival at the CTRC, participants will randomly receive either low-dose endotoxin (0.8 ng/kg of body weight) or placebo as an intravenous bolus over 30-60 seconds. NIH will provide reference endotoxin humans (E. coli group O:113). Throughout the study protocol lasting up to 12 hours, vital signs and blood sampling will be obtained every half hour for the first one hour, and then hourly thereafter. Placement of an intravenous catheter for the duration of the day has not been found to induce nonspecific increases in circulating levels of IL-6 or TNF .

## Randomization and allocation concealment

Randomization sequence will be generated via computerized random number generator in each group for endotoxin vs. placebo in a 1:1 ratio by the study biostatistician (RO) who has no contact with participants. Allocation concealment will be maintained confidential delivery of a secure and encrypted email to the CTTC pharmacy.

## Blinding

Participants will be aware that they are assigned to either endotoxin or placebo as the consent form states that participants would be assigned at random to either endotoxin or placebo as experimental conditions. Participants are blind to condition assignment, and they are also blind to the primary outcome of the study, namely depressed mood and depressive symptoms. Investigators and outcome assessors are blind to allocation.

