Ethics. All data were deidentified. Trial data monitoring and steering committees of the UCLA Clinical Translational Sciences Institute oversaw the study, which was undertaken according to the intention-to-treat principle. This study will adhere to the Consolidated Standards of Reporting Trials (CONSORT) reporting guideline.

Participants will be randomly assigned to receive either endotoxin or placebo in a 1:1 ratio in a between-subjects manner, stratified by insomnia status. Following administration of endotoxin (0.8 ng/kg body weight) vs. placebo, self- and observer rated measures of depressed mood will be assessed hourly over 12 hours (primary outcome) and self-rated measures of depressed mood and depressive symptoms every two hours over 12 hours (primary outcome). Additional secondary outcomes related to negative affective and positive affective responding will also be obtained as described below. We have found that older adults show a peak onset of depressed mood at 2 hours, similar to young adults and will explore the presence of delayed termination of response in older adults; hence protocol duration will last 12 h, as compared to 6 h as was previously used in the study of adults. Other secondary outcomes including assessment of physical symptoms, social dimensions, and inflammatory activity will be assessed as described in the detailed procedures below.

A between-subject parallel design will be used for the following reasons: 1) the proposed study involves endotoxin administration, and in a hypothetical crossover design, subjects who experience aversive sickness symptoms from endotoxin (possibly also from placebo due to expectation) might drop out, which would introduce bias and invalidate the results; 2) the effect of endotoxin on affective responding and inflammation might not resolve between two cross-over sessions of the experimental protocol; 3) repeated exposure to behavioral tests of affect responding might alter responses; 4) two cross-over sessions of the experimental protocol have higher subject burden.

Because the administration of endotoxin in this experimental protocol is designed to mimic the increases in plasma cytokines reported in chronic low-grade inflammatory conditions (i.e., 2-

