## Participants

### Recruitment of participants:

Given our focus on community-dwelling older adults, we employ survey-based, age-targeted sampling methods, which involve obtaining a list of telephone numbers and mailing addresses of households with at least one person aged 60 years or older from the Genesys Sampling Systems (Fort Washington, PA) or from the UCLA Clinical and Translational Science Institute (CTSI) Informatics Program. First, the Genesys Sampling System is a company that has been engaged in supporting various national surveys. Genesys Sampling Systems maintains a bimonthly updated database of all available listed telephone households in the US within a specified area. For this study a list of 5,000 households is purchased every 3 months. Initial contact is made using UCLA Institutional Review Board (IRB) approved recruitment brochures and letters, which inform potential participants of the study (i.e., a research study to examine “Sleep and Healthy Aging Research in Depression,” SHARE-D) and invite them to call a hotline number if interested. A follow-up phone call is made to confirm receipt of the letter, and a phone eligibility survey is completed if the participant is interested. This two-step method

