increases overall response rate and reduces interviewer time by 80% compared to a random-digit-dial sample surveys. Second, we obtained listing of persons aged 60 to 80 years who were enlisted in the UCLA Healthcare System, using the UCLA CTSI Informatics Program. This program queries xDR – a clinical data warehouse system containing data from UCLA’s CareConnect (Epic) Electronic Health Records (HER) linked with to older adult legacy systems and other sources. In addition to age-targeted sampling methods, the UCLA CTSI Informatics Program identifies those persons who have expressed interest in participating in research. Data from the UCLA CTSI Informatics Program are extracted every 6 months, including demographic and contact information. As noted above, participants are first contacted by brochure and letters, with follow-up phone contact. The survey sample for Genesys Sampling Systems and the CTSI Informatics Program are limited to households living within a 15 mile radius of the UCLA Westwood Campus, given the logistics of assessment and transport to UCLA for baseline assessment and the experimental protocol. We have employed sampling methods similar to those described for other randomized controlled trials that have enrolled older adults with insomnia as previously reported.

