## **Safety monitoring plan**

We have extensive experience with all aspects of the endotoxin vs. placebo inflammatory challenge and have administered endotoxin dose 0.8 ng/kg in over 150 adult participants (20-65 y) with no evidence of adverse events (AEs). Other studies have found that endotoxin dose 0.8 ng/kg can be administered in older adult subjects with no adverse effects . However, a 2.5-fold increase in the endotoxin dose to 2.0 ng/kg results in greater increases in proinflammatory cytokines, fever responses, and hypotension in older adults (61-69 years) as compared to young adults (20-27 years, unpublished data).

Safety monitoring is actively conducted throughout the study with hourly questions about physical symptoms and monitoring of vital signs. In addition, participants undergo a phone interview 1 and 7 days after the experimental session, in which there is active querying about physical symptoms, and evaluation of depressive symptoms by the MADRS. Therefore, adverse events will be identified by continuous reporting, and reviewed by the Principal Investigator (MRI).

Participants are given a 24-hour telephone number for calling the physician should feelings of depression or suicidal thoughts emerge in the 7 days following the protocol. In the event that significant medical or psychiatric problems are encountered, the study blind will be broken so that appropriate medical treatment will be provided.

The Principal Investigator has also designated appropriately qualified personnel to periodically perform quality assurance checks during and after the study. Such monitoring provides the opportunity to evaluate the progress of the study and to obtain information about potential problems. The monitor will assure that data are accurate and in agreement with any paper source documentation used, verify that subjects' consent for study participation has been properly obtained and documented, confirm that research subjects entered into the study meet inclusion and exclusion criteria, verify that study procedures are being conducted according to the protocol guidelines, monitor review AEs and serious adverse events (SAEs), and assure that all essential documentation required by Good Clinical Practices (GCP) guidelines are appropriately filed. At the end of the study, the monitors will confirm that the site has the appropriate essential documents on file, and advise on storage of study records.

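### The Protocol says participants are blind to the depression outcome, but its own recruitment letters name depression as the subject of the study

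*Protocol*

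**What the plan says.** The Blinding section of the Protocol makes three separate statements. On allocation to endotoxin or placebo, "Participants are blind to condition assignment". On the outcome, "they are also blind to the primary outcome of the study, namely depressed mood and depressive symptoms". On staff, "Investigators and outcome assessors are blind to allocation".

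Under Recruitment of participants, the first contact is by IRB-approved brochures and letters "which inform potential participants of the study (i.e., a research study to examine" the named topic, "Sleep and Healthy Aging Research in Depression". The second source, the health-system list, is approached in the same way: "participants are first contacted by brochure and letters, with follow-up phone contact".

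The primary outcome (Outcomes, Primary outcome) combines the POMS, which brings in self-rated depressed mood, with the observer-rated MADRS. Both are repeated over up to 12 hours. The key results (Statistical analysis) are the main effects of group and condition and their interaction.

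**The concern.** The outcome that participants are said not to know about is the topic printed in the study's name. If the clause stays, a report that repeats it will claim a protection that the Protocol does not provide.

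The consequence is specific to this design. Condition is randomised, but insomnia status is not, and people know how they sleep. Someone with insomnia who is told the study concerns sleep and depression may expect a mood change that a good sleeper does not expect. Blinding to endotoxin or placebo does nothing about that difference, because it lies between the groups and not between the arms. If participants also guess from feeling ill that they received endotoxin, the added expectation could fall mainly on those with insomnia who received endotoxin. A bias of that shape looks like the interaction the trial is designed to detect.

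**Working it through.** **Text check.** The plan gives no figure to reproduce on this point, so the first step is to set the statements side by side.

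1. What is claimed: participants do not know that depressed mood and depressive symptoms are the outcome (Blinding).
2. What is disclosed: the study name, containing both sleep and depression, goes to potential participants in the brochures and letters. Both listed recruitment sources use this first contact (Recruitment of participants).
3. Whether something offsets the disclosure: no cover story for the study's purpose is described. The only deception mentioned is for the Cyberball task (Secondary outcomes, social domain).
4. Other cues: the telephone screen asks about depression (Screening Eligibility), mood is rated repeatedly through the session (Trial Design), and a telephone number is supplied "should feelings of depression or suicidal thoughts emerge in the 7 days following the protocol" (Safety monitoring plan). These are weaker evidence. The screening questions serve exclusion and identify no outcome, and the Protocol does not say when the number is handed over. The contradiction between items 1 and 2 does not need them.
5. What is left intact: neither the masking of condition nor the masking of assessors is undone by the study's name.

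**Where expectation would enter the model.** Let d be the shift in POMS depression, in SD units, that expectation adds in each cell (I = insomnia, C = control; E = endotoxin, P = placebo). The bias in the interaction is

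(d_IE − d_IP) − (d_CE − d_CP).

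- The same shift in all four cells gives no bias in the interaction and none in the group effect.
- A shift b in both insomnia cells gives no bias in the interaction, and b in the group main effect.
- A shift b in both endotoxin cells gives b − b = 0 in the interaction.
- A shift b in the insomnia-endotoxin cell only gives b in the interaction. This requires that participants infer their condition.

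**Sensitivity calculation for the last case.** Inputs from the Protocol: 60 with insomnia and 100 controls, randomised 1:1 within group, so cells of 30, 30, 50 and 50; two-sided 5% test. Assumptions: outcome SD of 1, a contrast at one time point, no true interaction, and b between 0.2 and 0.5. The Protocol gives no value for b.

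SE = √(1/30 + 1/30 + 1/50 + 1/50) = √0.1067 = 0.327 SD.

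Rejection probability = P(Z > 1.96 − b/SE) + P(Z < −1.96 − b/SE).

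| b (SD) | b/SE | Rejection probability |
|---|---|---|
| 0 | 0 | 0.050 |
| 0.2 | 0.61 | 0.094 |
| 0.3 | 0.92 | 0.151 |
| 0.5 | 1.53 | 0.334 |

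The row b = 0 also covers equal demand in both endotoxin cells.

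**The case against.** A reader might infer that the self-rated primary outcome has no effective blinding at all. The documents do not support that. The main protection for the randomised comparison is that participants do not know their condition, and the study's name leaves that in place. Knowing the topic is also not the same as knowing which of many measures is primary: the session includes facial emotion, reward, social, cognitive, physical-symptom and cytokine measures. Part of the primary outcome, the MADRS, is rated by assessors stated to be blind to allocation. All of this stands. It limits the consequence but does not rescue the clause, which claims blindness to depressed mood and depressive symptoms themselves and not merely to the choice of primary scale.

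A reader might also infer that sickness symptoms reveal the allocation. The Trial Design section mentions "subjects who experience aversive sickness symptoms from endotoxin", but the sentence concerns a crossover design that was not adopted, and it adds that placebo recipients may feel ill through expectation too. Nothing in the Protocol shows how often participants would guess correctly at this dose. Unmasking through symptoms is plausible and remains a condition of the argument, not an established fact.

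Third, the error rates depend on a value of b with no source and on placing all of it in one cell. Controls receive the same letters and the same challenge, and with equal demand the inflation of the interaction is nil. The planned analysis is also a repeated-measures mixed model, not a single-time contrast. The figures show sensitivity only and are not an estimate.

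Finally, a neutral name would leave the screening questions and the mood ratings in place. That is correct, so renaming can weaken the cue but cannot by itself make the present clause true.

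**Conclusion.** The contradiction holds: the Blinding section asserts an outcome masking that the recruitment section contradicts. That conclusion rests on the text alone. It does not depend on the letters or the consent form, which are not shown.

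The consequence is conditional. The group main effect on self-rated mood is exposed because group is not randomised and condition blinding does not cover it. The interaction is exposed only if participants infer their condition and then respond differently according to insomnia status. The size is unknown. For the interaction the range runs from no inflation under equal demand in both endotoxin cells to a rejection rate of about 9% to 33% under an assumed shift of 0.2 to 0.5 SD confined to the insomnia-endotoxin cell, at a single time point. The Protocol describes no question on guessed condition or perceived purpose, so as described the trial could not tell afterwards where in that range it lies.

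**What to change.** 1. In the Blinding section, delete the clause on the primary outcome, or replace it with a statement of what is actually concealed, for example the hypothesis or which endpoint is primary. Do not report outcome blinding for anyone recruited under the current name. Leave the statements on condition and assessors as they are.
2. In future brochures, letters and telephone scripts, use a neutral name that does not mention depression. Leave the disclosure of risks in the consent form unchanged.
3. At the end of the session, ask each participant which condition they think they received and what they think the study is about. Report the answers descriptively by group and condition. Do not use them to split the test of the interaction. They are collected after randomisation and after 12 hours of mood ratings, so endotoxin and mood can themselves affect them, and a comparison within such subgroups is no longer randomised.

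The cost is an IRB amendment to the recruitment wording and two extra questions, with no added participants. The drawback for the sponsor is a less favourable blinding statement.
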